**Fig. 1 Fig1:**
[figure not shown]
OOC risk prediction tool (OOC-RPT)

In step one of our OOC-RPT—“Triage”—all MUHC PLHIV are automatically classified daily as either high risk (red), intermediate risk (yellow), or low risk (green). These risk categories are informed by patients’ clinical characteristics. The OOC-RPT categories determine priority for re-engagement and are informed by the risk of disease progression. Patients are then classified as potentially OOC, based on time since their last appointment. Additional file 1 details the evidence supporting the use of these three categories and related criteria.

In step two—“Nurse Validation”—patients identified as potentially OOC are reviewed and confirmed as such by nurses. The need and urgency for re-engagement is determined based on risk category, information contained within the patient’s chart, and clinical judgement. Nurses’ knowledge of patients’ sociodemographic, psychosocial, and clinical factors, travel plans, shared care or other care arrangements, homelessness, mental illness, and/or chronic illness will help inform the confirmation of OOC status. All information related to follow-up of OOC patients will be documented in the clinic’s electronic medical record database, called RISQ (Réseau d’Informations Scientifiques du Québec).

The OOC-RPT will be programmed into RISQ to automate identification of OOC patients and provide a real-time list of OOC patients. Patients will be listed from high to low risk, helping nurses prioritize re-engagement efforts.

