### Core element II: Contacting OOC patients

Clinic nurses will telephone patients using available contact information (RISQ, other hospital databases). They will receive a half-day of training from an expert in motivational communication, an essential skill for motivational interviewing. This training will help nurses encourage re-engagement through effective questioning, empathy, non-judgemental curiosity, guiding language, and adapted messaging [18]. This training is intended to provide nurses with additional skills or to strengthen existing skills for phone calls. It will be used at their discretion.

Patients who are reached by telephone will be scheduled for an appointment within timeframes dependent on their OOC-RPT risk category. However, earlier follow-up may be necessary as determined by clinical judgement. Patients in the high-risk category will be scheduled to be seen by a clinic nurse within 24-48 hours for basic primary care and phlebotomy (laboratory testing), and with their regular physician provider within one week of the nursing visit, for a full clinical assessment. Should the clinical situation suggest a need for more urgent care, the patient will be assessed by the walk-in physician on the same day as the nursing visit. Patients in the intermediate-risk category will be scheduled for an appointment within approximately two to four weeks of the telephone call, while patients in the low-risk category will be seen within four to six weeks. Patients who miss a scheduled appointment will be contacted the same day and provided another appointment, within timeframes depending on their risk category.

Attempts to contact patients will be made every 1, 2, and 4 weeks, for the high-, intermediate-, and low-risk categories, respectively. This pattern will be repeated until patients are contacted. Attempts to re-engage unreachable OOC patients will continue for up to 6 months (based on the maximum time a person can be outside of Quebec and still retain health care coverage), after which no further contact attempts will be made [19]. Nonetheless, these patients will remain on the OOC list until they return to care or until there is sufficient information to determine their care status. In all cases, nurses can modify the contact frequency and/or period based on individual patient factors.

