#### Outcomes and related measures

##### Effectiveness

Information to evaluate changes in interim effectiveness outcomes over time will be collected automatically using RISQ and will be extracted for analysis at specific time points during the study (see Table 2). Interim effectiveness refers to effectiveness between the time points in Table 2, as opposed to cumulative effectiveness, which refers to overall effectiveness for the implementation or sustainability phases. These interim effectiveness outcomes include the number of patients identified and confirmed as OOC by nurses. Among OOC patients, we will report the number of patients contacted, successfully re-engaged, and not re-engaged, as well as reasons for lack of care re-engagement. For each OOC-RPT risk category, and overall, we will also provide the number of contact attempts needed to re-engage patients, time to re-engagement, and other clinical and sociodemographic information routinely collected in RISQ.

**Table 2 Tab2:** Data collection schedule

	Pre-implementation	Week 1	Week 2	Week 3	Week 4	Month 2	Month 3	Month 6	Month 12	Month 15
Effectiveness					d	d	d	d	d	d
Feasibility	a, c				a, c	a, c	a, c	a, c	a, c	c
Acceptability	a, c				a, c	a, c	a, c	a, c	a, c	c
Adoption	a, c				a, c	a, c	a, c	a, c	a, c	c
Fidelity	b, c	b	b	b	b, c	b, c	b, c	b, c	b, c	c

a) 36-item questionnaire; b) fidelity checklist; c) focus group; and d) RISQ

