#### Participants

All MUHC patients in the RISQ database during the 12-month implementation phase and the first three months of the sustainability phase will be included in analysis i). For analysis ii), we will retrospectively apply the OOC-RPT, excluding the nurse validation step, to patients in the year prior to implementation in order to create a pre-implementation comparison group. Thus, we will include all patients categorised as OOC by the OOC-RPT from one year prior (2017-2018) and to the end of the implementation phase (late 2019) in this analysis. Patients labelled as OOC before or after this time frame will receive the Lost & Found intervention, but will be excluded from the analysis because they did not become OOC within the time frame of the analysis. Based on the number of patients who were identified as not having had care appointments in 2016, we estimate approximately 25–30 patients will be identified as potentially OOC each month during the implementation of Lost & Found. In analysis iii), MUHC patients categorised as OOC from three months before the end of the implementation phase to the end of the sustainability phase (three months) will be included.

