where *R* is a count of number of patients re-engaged into care, *Imp* is a dummy variable, where *Imp* = 1 indicates that the patient was OOC during the implementation phase and 0 for the pre-implementation phase, *Sex* accounts for the possible differences in the proportion of men and women in the pre-implementation or implementation phases, *Age* accounts for differences in the ages of patients between the two periods, and *Canada* accounts for differences between the two periods for the proportion of patients born outside of Canada, which may be of concern given a recent influx of refugees into our clinic. *log(C)* is considered the “offset” in the Poisson regression model, where *C* is the number of patients OOC over the two periods. We assume that Lost & Found will not impact the rate at which patients are categorised as OOC in the implementation phase and will verify this assumption prior to conducting the analysis. Potential other variables for inclusion in the model will be selected to adjust for possible temporal shifts in the patient population (i.e. factors that could affect engagement in care.) Due to lacking information in the pre-implementation period (e.g. number of patients confirmed as OOC by nurses, information about re-engagement efforts) it is not possible to consider the relative overall effectiveness of each core element.

The overall effect of the intervention and implementation strategy on the proportion of re-engaged OOC patients will be determined from the log of the *β*_*1*_ coefficient, providing a risk ratio for the probability of re-engaging OOC patients through the use of Lost & Found.

We did not conduct a sample size calculation due to uncertainty for several study parameters, including effect and sample sizes. The results of this analysis will inform power calculations for a larger study. Thus, while a statistically significant result would suggest that Lost & Found is viable for further evaluation, a statistically non-significant result would not necessarily rule it out since such a result may only be due to insufficient power.
iii)Pre-post analysis: Sustainability phase

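### Equation 1 adjusts for sex, age and birthplace but not for the OOC-RPT risk category, which can be derived for flagged patients in both periods

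*Protocol article*

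**What the plan says.** Aim 2, Data analysis, ii) prints a Poisson model with robust variance. Its terms are the period indicator (Imp), Sex, Age and Canada, plus an offset. Each covariate is justified as handling a difference between the two periods; age, for example, "accounts for differences in the ages of patients between the two periods". The text then leaves room for more: "Potential other variables for inclusion in the model will be selected to adjust for possible temporal shifts in the patient population". Analysis iii) uses the same equation to compare the sustainability phase with the last three months of implementation.

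Risk category is not among the terms. Under Core element I, "all MUHC PLHIV are automatically classified daily as either high risk (red), intermediate risk (yellow), or low risk (green"), and time since the last appointment is applied after that. For the comparison year, Aim 2, Participants says "we will retrospectively apply the OOC-RPT, excluding the nurse validation step, to patients in the year prior to implementation". Under Core element II the category governs how the programme works: "Attempts to contact patients will be made every 1, 2, and 4 weeks, for the high-, intermediate-, and low-risk categories, respectively", and patients who are reached are "scheduled for an appointment within timeframes dependent on their OOC-RPT risk category".

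The category is used descriptively. Aim 1, Effectiveness says: "For each OOC-RPT risk category, and overall, we will also provide the number of contact attempts needed to re-engage patients". Analysis i) of Aim 2 reuses those measures. No pre-post comparison by category is described.

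**The concern.** Analysis ii) is a non-randomised comparison of two calendar years. A statistically significant difference in re-engagement is the stated sign that the intervention works, and it is also said to suggest viability for further evaluation. The estimate therefore depends on the two groups being alike, or made alike by adjustment, in whatever drives return to care.

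The article gives reasons to count clinical risk among those drivers. The Background criticises definitions of being out of care that ignore clinical factors, and it cites a clinical risk tool that predicted missed appointments. The Conclusions describe the study's own definition as built on characteristics believed to be linked to care interruption. The category is assigned before any contact attempt, so at first flag it is a baseline variable and not a consequence of the intervention. Leaving it out of the printed model leaves a measurable source of confounding uncontrolled.

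**Working it through.** The plan gives no sample size, power, effect size, risk mix or return rate by category, so there is no figure of its own to reproduce. The check has three parts.

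**1. Is the category available in both groups?** In the implementation year it is assigned daily by step 1. In the prior year it comes from running the tool retrospectively without nurse validation. Step 1 defines both groups in analysis ii), so each patient in that analysis can be given a category.

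**2. How many patients are there to support it?** Aim 2, Participants expects 25 to 30 potentially out-of-care patients a month during implementation.
- Implementation year: 12 × 25 = 300 to 12 × 30 = 360.
- Each three-month period in analysis iii): 3 × 25 = 75 to 3 × 30 = 90, before nurse validation removes some.

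A three-level category needs two indicator terms.

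**3. What does omission do when there is no true effect?** With return probability p_k in category k and mix w_k, the risk ratio without a risk term is

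RR = Σ w_k(implementation) p_k / Σ w_k(prior) p_k.

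All inputs here are assumptions. The prior-year mix is 30/30/40% for high/intermediate/low risk, and 10 or 20 points move from high to low risk.

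| Return rates, high/int./low | Shift | Prior year | Implementation year | RR |
|---|---|---|---|---|
| 30/40/50% | 10 points | 0.09 + 0.12 + 0.20 = 0.41 | 0.06 + 0.12 + 0.25 = 0.43 | 1.05 |
| 30/40/50% | 20 points | 0.41 | 0.03 + 0.12 + 0.30 = 0.45 | 1.10 |
| 20/40/60% | 10 points | 0.06 + 0.12 + 0.24 = 0.42 | 0.04 + 0.12 + 0.30 = 0.46 | 1.10 |
| 20/40/60% | 20 points | 0.42 | 0.02 + 0.12 + 0.36 = 0.50 | 1.19 |

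With no shift, numerator and denominator are equal and RR = 1.

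A simulation of the robust-variance Poisson model (800 runs, 300 patients per year, same assumptions) agrees. It contained no sex, age or birthplace, so the shift stands for the part those terms would not absorb.
- Without the risk term, two-sided rejection at 5% was about 6% and 19% for the first pair of rows and about 15% and 50% for the second pair.
- With the risk term, the RR returned to about 1.00 and rejection to about 4 to 6%.
- With no shift, both models gave an RR of about 1.00.

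The sign depends on the gradient. Suppose instead that high-risk patients return most, at 70/50/35%. A change in mix from 20/30/50% to 30/30/40% moves the crude rate from 0.140 + 0.150 + 0.175 = 0.465 to 0.210 + 0.150 + 0.140 = 0.500, RR 1.08. The reverse change gives 0.465/0.500 = 0.93. The bias can favour the intervention or hide its effect.

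**The case against.** The strongest reply is that Equation 1 is not a closed list. Its text allows further variables for shifts in the patient population, and risk category fits that description. The final list and its lock date normally sit in an analysis plan, which is not shown. As far as closing the list goes, this stands: the open clause alone would be missing detail, not an error. It does not answer the narrower point. The article prints the model and defines its terms, yet the study's own stratifier is not one of them.

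Several stronger readings are tempting, and the documents do not support them:
- *The refugee influx passes straight into the period effect.* The Canada term is there because of that influx and covers part of it. Only a shift in risk not captured by birthplace, age and sex remains.
- *The contact and booking rules make the category a confounder.* Those rules apply only under Lost & Found, and nurses may vary contact frequency. They show how the effect could differ by category, not that the years are unbalanced.
- *The category is already on record for both years.* For the prior year it is derived retrospectively.
- *Covariates will be picked for significance.* The text ties additions to population shifts and says nothing of selecting them on results.

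It is also fair that this is a pilot, that Limitations concedes uncontrolled confounding in general terms, and that a non-significant result is not taken to rule the intervention out. These points lower the stakes. They are not a reason to leave out a covariate that can be measured.

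**Conclusion.** The point holds in a limited form. Equation 1 should name the OOC-RPT risk category, because step 1 yields it at first flag in both periods and the article regards its components as related to staying in care. Bias in the risk ratio requires two things together: a difference in risk mix between the periods beyond what sex, age and birthplace capture, and return to care that differs by category. The documents show neither, and they do not fix the direction or size. Under the assumed rates the spurious risk ratio is about 1.05 to 1.19 for a 10 to 20 point shift, and nil without a shift; the upper end needs both a large one-year shift and a threefold gradient. A reader might infer that the planned estimate is known to be biased in favour of the intervention. That does not follow.

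**What to change.** Add OOC-RPT risk category at the first out-of-care flag to Equation 1 as a named three-level covariate for analysis ii). Derive it with one fixed version of the tool in both periods, because the section on promoting adaptability lets the tool change during implementation and categories from different versions would not be comparable. Use the same term in analysis iii), noting that about 75 to 90 flagged patients per period are expected before nurse validation, so the adjusted estimate will be less stable there.

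Report the pre-post risk ratio within each category descriptively. A main-effect term removes imbalance but does not show where the effect lies, and the reporting by category planned under Aim 1 contains no pre-post contrast.

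The cost is two extra parameters. No new data are needed, since the tool is already to be run on both years.

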This analysis is similar to the one detailed in ii) but compares effectiveness during the three-month sustainability phase to the last three months of the implementation phase. The analysis also differs in that the nurse validation step of the OOC-RPT will be included in each arm since manual changes to follow-up status is possible in both arms. We hypothesise that few changes will be made to peripheral components of Lost & Found in the last three months of the implementation phase, suggesting the intervention will be comparable to that which is delivered in the sustainability phase.

The same model (Equation 1) will be used to assess short-term sustainability of Lost & Found, where *Imp* = 1 indicates that the patient was OOC during the sustainability phase and 0 for the last three months of the implementation phase. A finding of no statistically significant difference in the probability of re-engagement for OOC patients in the implementation or sustainability phases will suggest short-term sustainability of Lost & Found.

All analyses will be conducted using R statistical software.

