## Limitations

There are limitations to this pilot study. Firstly, our assessment of the implementation strategy is limited by our lack of a control group and our small sample (*n* = 4) of nurses. While our cumulative effectiveness and sustainability evaluations include control groups, pre-post analyses are subject to bias from uncontrolled confounding. Secondly, available clinical databases have insufficient information to accurately determine whether patients are truly OOC, which could inflate the number of patients identified as such. This is consistent with other studies finding that most patients identified as OOC are not actually OOC [35–37]. In our pre-post evaluations, this would have the effect of increasing the total number of OOC patients (the denominator) in each arm, biasing our effect estimates towards the null (i.e. non-differential bias). Finally, our assessment of sustainability is limited to three months, limiting our capacity to report on changes in Lost & Found use and related effectiveness over the long-term. Importantly, these limitations are offset by the variety of both intervention- and implementation-specific qualitative and quantitative assessments, as well as mixed-methods analyses. Together, we will have rich data for evaluating and reporting on the viability of implementing this intervention for the purposes of undertaking a larger scale and controlled evaluation.

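### The sustainability analysis reads a non-significant difference between two small three-month groups as evidence of sustainability, so a real moderate decline would usually pass as sustained

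*Protocol article*

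**What the plan says.** Short-term sustainability is part of Aim 2. In the Protocol article (Aim 2, Data analysis, iii) Pre-post analysis: Sustainability phase), the analysis "compares effectiveness during the three-month sustainability phase to the last three months of the implementation phase", using the same Poisson model with robust variance as analysis ii). Patients enter after nurse validation in both windows. The interpretation is fixed in advance: a finding of "no statistically significant difference in the probability of re-engagement for OOC patients in the implementation or sustainability phases will suggest short-term sustainability". No margin, interval criterion or precision target is given.

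In analysis ii), the article states that no sample size was calculated and cautions that a non-significant finding would not rule the intervention out, because "such a result may only be due to insufficient power". Analysis iii) carries no such caution.

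On numbers, the Aim 2 Participants section says "we estimate approximately 25–30 patients will be identified as potentially OOC each month". The Limitations section adds that other studies found that "most patients identified as OOC are not actually OOC". It names the three-month duration as a limitation, but not the way the test is read.

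**The concern.** A test of equality that fails to reject says only that the data are compatible with no difference. They may be equally compatible with a substantial loss. Here the favourable conclusion is attached to the failure to reject, so smaller groups make that conclusion more likely whatever the true re-engagement rate has done.

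The two analyses are also read inconsistently. Non-significance in the twelve-month comparison is put down to possible lack of power. In a comparison with about a quarter of the patients, it counts as the positive result.

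At stake is the sustainability conclusion of Aim 2, which informs whether a multisite stepped-wedge trial is viable.

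**Working it through.** The plan states no power, sample size or margin for analysis iii), so there is no figure of its own to reproduce.

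**Inputs from the article**
- Inflow of 25–30 potentially OOC patients per month (Aim 2, Participants).
- Two three-month windows: 3 × 25 = 75 to 3 × 30 = 90 per arm, before nurse validation. Validation can only lower this.
- For comparison, a twelve-month window in analysis ii): 12 × 25 = 300 to 12 × 30 = 360, before repeat events are removed.
- A risk ratio (RR) from a Poisson model with robust variance.

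**Assumptions, because the article gives no figure**
- Two-sided 5% test.
- Re-engagement of 30–50% in the last three implementation months.
- About 45 per arm after validation, that is, half of 90 confirmed. The Limitations section makes this plausible but gives no local confirmation rate.
- No covariate adjustment.

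**Formula.** For two groups of size n with rates p0 and p1, the model's test reduces to a Wald test on the log RR, with SE² = (1−p0)/(n·p0) + (1−p1)/(n·p1). With z = |log(p1/p0)|/SE, power is Φ(z − 1.96) + Φ(−z − 1.96). One minus power is the chance that a real fall is read as sustained.

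*Worked case:* n = 75, 30% → 22.5%. SE² = 0.70/22.5 + 0.775/16.875 = 0.0770, so SE = 0.278. |log 0.75| = 0.288, so z = 1.04, power = 0.18 and the chance of non-significance is 82%.

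| True change | n = 75 | n = 90 | n = 45 |
|---|---|---|---|
| 30% → 22.5% (25% relative fall) | 82% | 79% | 87% |
| 50% → 37.5% (25% relative fall) | 67% | 61% | 78% |
| 30% → 15% (halving) | 44% | 36% | 62% |
| 50% → 25% (halving) | 15% | 9% | 36% |
| 50% → 30% (20 points) | 32% | 24% | 53% |

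Entries are the probability of a non-significant result.

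**Precision when the observed rates are identical.** The 95% CI for the RR is exp(±1.96·√(2(1−p)/(n·p))):
- n = 75, p = 30%: 0.61–1.63
- n = 90, p = 50%: 0.75–1.34
- n = 45: 0.53–1.88 (30%) or 0.66–1.51 (50%)

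Even a perfect match would leave a relative loss of 25% to 47% inside the interval, depending on the case, and the rule would still report sustainability.

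**What a margin would demand.** With no true change, the chance that the lower limit exceeds 0.80 is Φ(−log 0.80/SE − 1.96). This is 14–32% at 75–90 per arm and 10–18% at 45. At n = 75 and 30%, the observed RR would have to reach about 0.80 × exp(1.96 × 0.249) = 1.30.

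**The case against.** The strongest defence has three parts.

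- **It is a hedged sentence in an acknowledged pilot.** The rule says only that the result will suggest sustainability, in a study that admits it made no sample size calculation. This is true, but small size justifies an imprecise answer, not a favourable one. The article applies that reasoning to analysis ii) and not to iii).
- **Other evidence bears on sustainability.** Analysis i) describes the sustainability phase, the month-15 focus group concentrates on it, and the model yields a risk ratio. The explicit viability criterion in the mixed-methods section rests on implementation scores supported by focus groups. This stands: no go/no-go decision hangs on analysis iii) alone, and it would be wrong to say that the whole sustainability conclusion rests on one p-value.
- **The full plan may specify intervals.** It may, and their absence from an article would not be a finding. The point is the rule that the article does state.

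A reader might also infer that the pilot will usually report success even after a sharp drop. The numbers do not support that in general. At 75–90 per arm, a halving is missed in 36–44% of trials from 30% and in 9–15% from 50%, so it is more often detected than not. At 45 per arm, a halving from 30% would usually be missed (62%), but one from 50% would not (36%). The 45 is itself an assumption.

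**Conclusion.** The rule is wrong as written. It takes absence of evidence as evidence of sustainability, without a margin, and conflicts with the article's own warning about power.

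It would often report sustainability despite a real decline, and usually do so when the decline is moderate: in 61–82% of trials for a 25% relative fall at 75–90 per arm, and in 78–87% at 45. For a halving, the figures are 9–44% and 36–62%.

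These sizes depend on the assumed 30–50% reference rate, the 5% two-sided level and, for the smaller arms, the assumed confirmation rate. The flaw in the logic depends on none of them.

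**What to change.** Delete the sentence that equates non-significance with sustainability. Report the re-engagement RR, sustainability phase against the last three implementation months, with its 95% CI. Claim short-term sustainability only if the lower limit lies above a retention margin that the investigators choose and record before seeing the data. Otherwise report the result as inconclusive.

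The core change is to wording and needs no new data. Its cost is candour: inconclusive is the likely verdict, and a margin near RR 0.80 would rarely be met even if nothing had changed.

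If the sustainability phase is also compared with the pre-implementation year, both periods should use patients flagged by step 1 of the OOC-RPT, without nurse validation, as in analysis ii). Validation was not possible before implementation, and mixing validated with unvalidated patients would bring in the differential bias that analysis ii) is designed to avoid. This optional comparison requires building a separate step-1 patient set for the sustainability phase.
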